## Abstract

**Abstract:**

**Introduction:**

Care (Education) and Treatment Reviews (C(E)TRs) are intended to reduce unnecessary psychiatric hospital admission and length of stay for people with intellectual disability and autistic people. The use and impact of C(E)TRs have not been systematically evaluated since their introduction in England in 2015. The aims of this study are to describe the demographic and clinical profiles of people who receive a community C(E)TR and to investigate their effects on admission, length of hospital stay and clinical and functional change.

**Methods and analysis:**

We will conduct a retrospective cohort study using de-identified data from electronic health records derived from two large National Health Service mental health providers in London, England, including one replication site. Data will be extracted using the Clinical Record Interactive Search (CRIS) tool for all people with recorded intellectual disability and/or autism who received mental healthcare from 2015. We will identify community C(E)TR events using keyword searches. Community C(E)TRs will be examined in two ways: (1) In a community cohort, we will capture data in the 6-month periods before and after a community C(E)TR and compare this to a matched control group and (2) In a hospital cohort, we will compare groups who did and did not receive a community C(E)TR prior to their admission. We will describe the socio-demographic and clinical profiles of each group and their health service use, and compare C(E)TR and no C(E)TR groups using t-tests (or a non-parametric equivalent). The primary outcomes are admission to a psychiatric hospital (community cohort) and length of psychiatric hospital admission and clinical change (hospital cohort). Admission to psychiatric hospital will be estimated using propensity score weighting and difference-in-differences methods. Cox’s proportional hazard model will be used for length of hospital admission and repeated-measures analysis of variance (ANOVA) will be used to assess clinical change.

**Ethics and dissemination:**

Use of CRIS to examine de-identified clinical data for research purposes has overarching ethical approval. This study has been granted local approval by the South London and Maudsley CRIS Oversight Committee. Findings will be disseminated in an open-access peer-reviewed academic publication, at conference presentations, and to service users and carers in accessible formats.

STRENGTHS AND LIMITATIONS OF THIS STUDYThis study uses routinely collected health data, which represent real-world clinical practice and enables us to generate a relatively large cohort not biased by participant selection.The study will be undertaken in a large NHS Trust with a diverse catchment area.We will replicate the study in a second NHS Trust to provide evidence for the generalisability of the initial findings across a different population.The number of people in the dataset who have received a community Care (Education) and Treatment Review is unknown; if there are relatively few events, our dataset may be underpowered to demonstrate differences between those who do and do not receive the intervention (type 2 error).Electronic health record data are generated as part of routine clinical practice and may include missing data, which could limit our analysis.

## Introduction

 Reducing unnecessary psychiatric hospital admissions and length of hospital stay for people with intellectual disability and autistic people has been a focus of English national health policy since the scandal of abuse and neglect of patients at Winterbourne View Hospital in 2011.^1^ The Transforming Care programme was established to improve community health and social care for people with intellectual disability and autistic people and to reduce what had generally been considered to be an over-reliance on inpatient psychiatric services.^2^ A key element of Transforming Care has been the introduction of Care (Education) and Treatment Reviews (C(E)TRs), person-centred review meetings that aim to ensure the right support is provided.^3^ A community C(E)TR should be convened when a person with intellectual disability or an autistic person living in the community is considered at high risk of admission to a psychiatric hospital, either because of mental ill-health or because of an escalation in behaviours that challenge. C(E)TRs are chaired by a health commissioner and include an independent clinical expert and an expert-by-experience, often a family carer of a person with intellectual disability or an autistic person. This panel gathers information from the individual, their families and carers, and professionals, and produces a report and action plan following the C(E)TR with recommendations (eg, input from specialist professionals or health teams, provision of additional care, use of respite services) that can enable the person to remain living safely in the community. Where admission to hospital is considered necessary, the C(E)TR panel will define the purpose of the admission and encourage early discharge planning in order to minimise the length of the hospital stay. Inpatient C(E)TRs are convened at various points of a hospital admission; the current project investigates only C(E)TRs that are held in the community.

Little formal research has been carried out on community C(E)TRs, such as who receives them and when, and how C(E)TRs may influence health service use, including admission to hospital. By understanding the demographic and clinical profile of patients who do, and do not, have a community C(E)TR, it may be possible to develop targeted interventions to improve access to community C(E)TRs and ensure the potential benefits are available to everyone.

### Study aims and design

We will conduct a retrospective cohort study using a large dataset of real-world clinical data derived from Electronic Health Records (EHRs) to investigate who receives a community C(E)TR and the association of community C(E)TRs with patient outcomes and service use. This work includes two sub-studies:

#### Sub-study 1: community cohort

We will: (1) Examine the demographic and clinical profile of those who receive a community C(E)TR and (2) attempt to model the causal relationship of receiving a community C(E)TR on the risk of psychiatric hospital admission.

#### Sub-study 2: hospital cohort

For patients who are admitted to a psychiatric hospital, we will compare: (1) The demographic and clinical profile before admission, (2) length of stay in hospital and (3) clinical and functional improvement while in hospital, between those who had a community C(E)TR prior to their admission and those who did not.

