#### Sub-study 1: community cohort

Population, Intervention, Comparison and Outcome (PICO) framework (table 1).

**Table 1 T1:** Population, Intervention, Comparison and Outcome framework for sub-studies 1 and 2

	Sub-study 1	Sub-study 2
Population	People of any age with a recorded diagnosis of intellectual disability (ICD-10 code F7x), autism (ICD-10 code F84) or both, with at least 1 year of care under secondary mental healthcare services	People of any age with a recorded diagnosis of intellectual disability (ICD-10 code F7x), autism (ICD-10 code F84) or both, with at least 1 year of care under secondary mental healthcare services and an admission to a psychiatric inpatient ward for a period of at least 14 days
Intervention	Community C(E)TR	Community C(E)TR within 6 months prior to admission
Comparison	No community C(E)TR	Did not receive a community C(E)TR within 6 months prior to admission
Outcome		
Primary	Psychiatric hospital inpatient admission within 6 months of the community C(E)TR	Length of psychiatric hospital admission (days)
Secondary	Descriptive data and comparison of baseline demographics between intervention and comparison groups	Descriptive data and comparison of baseline demographics between intervention and comparison groups
	Descriptive data of 6 months pre-C(E)TR/post-C(E)TR (index date): neuropsychiatric symptoms, clinical variables and service use	Descriptive data and comparison of prehospital admission neuropsychiatric symptoms, HoNOS and service use Clinical and social functional improvement (change in HoNOS) while in hospital

C(E)TR, Care (Education) and Treatment Review; HoNOS, Health of the Nation Outcome Scales.

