#### Time-to-event analysis

Time-to-discharge (length of hospital admission) will be analysed using the Kaplan-Meier estimator.^19^ A Cox’s proportional hazards model will be used to estimate the HR for discharge,^20^ comparing those who received a C(E)TR to those who did not receive a C(E)TR for a follow-up period of 6 months after admission. This analysis will be adjusted for C(E)TR status prior to admission, age at admission, sex, ethnicity and relevant diagnosis at admission (intellectual disability with/without autism, or autism alone). Patients who die within 6 months of admission will be censored at the date of death, and patients who remain in hospital will be censored at the end of the 6 months.

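### Sub-study 2 compares length of stay only among admitted people, a group the C(E)TR is meant to change, so its hazard ratio cannot show an effect on length of stay

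*Protocol article*

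**What the plan says.** The abstract says that C(E)TRs "are intended to reduce unnecessary psychiatric hospital admission and length of stay for people with intellectual disability and autistic people" and gives an aim "to investigate their effects on admission, length of hospital stay and clinical and functional change". The main Introduction describes panel recommendations "that can enable the person to remain living safely in the community". It adds that where admission is needed the panel defines its purpose and encourages early discharge planning.

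Sub-study 1 addresses admission. Its primary outcome in Table 1 is "Psychiatric hospital inpatient admission within 6 months of the community C(E)TR", analysed with propensity weights and difference-in-differences.

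Sub-study 2 addresses length of stay: "For patients who are admitted to a psychiatric hospital, we will compare: (1) The demographic and clinical profile before admission, (2) length of stay". Under its Inclusion and exclusion criteria, the stay must be at least 14 days. Under Identifying cases and controls, exposure is a community C(E)TR in the 6 months before that admission. The Cox model is described as "comparing those who received a C(E)TR to those who did not receive a C(E)TR for a follow-up period of 6 months after admission". Besides C(E)TR status, it adjusts for age, sex, ethnicity and diagnosis. Pre-admission symptoms, HoNOS and service use are compared between the groups but are not in that model, and propensity weighting is described only for sub-study 1.

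The stated limitations include low power and missing data. Selection by admission is not among them.

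**The concern.** Admission happens after the exposure, and the exposure is meant to change it. A person whose admission was averted by a C(E)TR is missing from the C(E)TR group of sub-study 2. A similar person without a C(E)TR is admitted and counted in the comparison group. The two admitted groups can then differ in severity even if C(E)TRs had been handed out at random. The four adjustment variables include no direct measure of severity that could absorb the difference.

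The 14-day minimum is a second selection after exposure, and it acts on the outcome itself. A stay shortened to under 14 days leaves the analysis instead of counting as a success.

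At stake is how the results are read. A causal estimate for admission will stand beside a hazard ratio for discharge from a differently selected group, under an aim that speaks of effects on both. Policy readers could take that hazard ratio as evidence that C(E)TRs lengthen stay, shorten it or leave it unchanged, when it may reflect only who was admitted.

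**Working it through.** **Inputs.** The article gives no admission rate, length of stay, event count or target hazard ratio, and says the number of C(E)TRs is unknown. There is no plan figure to reproduce, so everything below is assumed in order to show direction and rough size:
- 60% of people are lower severity: 15% admission risk, median stay 30 days.
- 40% are higher severity: 45% admission risk, median stay 90 days.
- Stays are exponential, with one admission per person.
- C(E)TR is assigned at random (no confounding), and severity is not in the Cox model.
- Follow-up is censored at 182 days. The C(E)TR changes nobody's stay, so the true HR is 1.00.

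**Step 1: who is admitted.** Control admissions are 0.60 × 0.15 + 0.40 × 0.45 = 0.09 + 0.18 = 0.27, of which 0.18 / 0.27 = 67% are higher severity. If the C(E)TR averts half of the lower-severity admissions, the C(E)TR group has 0.045 + 0.18 = 0.225 admitted, of which 0.18 / 0.225 = 80% are higher severity. If it averts 75%, the figures are 0.0225 + 0.18 = 0.2025 and 89%. If it halves admissions in both groups, the share stays at 67%. If it halves only the higher-severity admissions, the share is 0.09 / 0.18 = 50%.

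**Step 2: discharge HR among the admitted** (simulation, 1,000,000 people per scenario; simulation error about 0.01).

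| Admissions averted | HR, all admissions | HR, stays of at least 14 days |
|---|---|---|
| None | 1.00 | 1.00 |
| 25% of lower severity | 0.95 | 0.95 |
| 50% of lower severity | 0.89 | 0.90 |
| 75% of lower severity | 0.81 | 0.84 |
| 50% in both groups | 1.00 | 1.00 |
| 50% of higher severity only | 1.16 | 1.15 |

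With 75% of lower-severity admissions averted, the median stay over all admissions is 79.5 days against 60.4, although nobody's stay was lengthened.

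**Step 3: a real benefit.** With a true HR of 1.2 and no effect on admission, the model gives 1.17 (severity is omitted, which pulls the estimate slightly towards 1). With 50% of lower-severity admissions averted it gives 1.04, and with 75% averted 0.97. The benefit is hidden.

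**Step 4: other assumptions.** Take a continuous severity score, admission risk cut from 30% to 20%, a median stay of 60 days at average severity and no effect on stay. The HR is 0.77 to 0.93 if averted admissions come from the milder half, 0.90 to 0.98 under a uniform shift on the logit scale, and 0.99 to 1.01 if risk falls by the same proportion at every severity.

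**Step 5: inpatient days per person in the 182 days after the index date.** If admissions are spread evenly over the window, mean days per admitted person are (1/λ)[1 − (1 − e^(−182λ))/(182λ)], where λ = ln 2 / median stay.
- Median 30: 1/λ = 43.28 and 182λ = 4.205, giving 33.1 days.
- Median 90: 1/λ = 129.84 and 182λ = 1.402, giving 60.0 days.

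Per person:
- Control: 0.09 × 33.1 + 0.18 × 60.0 = 13.8.
- 50% of lower severity averted: 0.045 × 33.1 + 0.18 × 60.0 = 12.3.
- 75% averted: 0.0225 × 33.1 + 0.18 × 60.0 = 11.5.
- 50% of higher severity averted: 0.09 × 33.1 + 0.09 × 60.0 = 8.4.

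This measure falls whenever admissions are averted, whichever they are. It falls here even though no stay changed, so it measures total burden and not duration.

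**The case against.** **The bias need not run one way.** A reader might infer that a C(E)TR which succeeds on admission will look worse on length of stay, so that the two outcomes pull against each other. The documents do not support that. They speak of unnecessary admissions, which makes averted short stays plausible, but they give no pattern by severity. A proportional reduction produces no bias, and averting mainly severe admissions produces apparent benefit. What stands is that the HR can mislead in either direction.

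**Stay among the admitted is a legitimate question.** Early discharge planning is a separate mechanism for people who are admitted, and inpatient days per person cannot isolate it, as step 5 shows. This objection stands. Inpatient days should supplement the sub-study 2 outcome and not replace it.

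**The plan is already mostly associational here.** Study aims and design speaks of "the association of community C(E)TRs with patient outcomes and service use", the sub-study 2 aim only compares, and the HoNOS analysis asks about association. That is fair and limits the point. The abstract's aim still claims effects on length of stay, and no limitation warns the reader.

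**Whole-cohort measures may already exist.** A reader might infer that nothing in the plan counts hospital days for everyone. That cannot be checked, because online supplemental table 2, which lists the service-use variables, is not shown. The economic extension also compares total cost per patient. However, the sub-study 1 descriptives are expressly given no causal interpretation, and cost is a composite.

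**A more severe remainder would be visible.** Pre-admission symptoms, HoNOS and service use are compared between the admitted groups. This helps interpretation, but the planned HR is not adjusted for them.

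**Conclusion.** The point holds on structure. The sub-study 2 groups are formed by an event after exposure that the exposure is intended to change, and again by a minimum of 14 days on the outcome. The planned adjustment does not address either selection. The discharge HR is therefore interpretable as an association among admitted patients and cannot support the abstract's aim of an effect on length of stay.

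The size is unknown. Under the two-class assumptions with no true effect, the HR ranges from 0.81 to 1.16 depending on which admissions are averted, and a true HR of 1.2 can appear as 0.97. All of this rests on assumed risks, stays and severity patterns, and on severity affecting both admission and stay. Sub-study 1's admission analysis is not affected. This is a low-cost improvement, not a reason to drop the hospital cohort.

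**What to change.** 1. In the sub-study 1 cohort, add a secondary outcome: psychiatric inpatient days in the 6 months (and, in the extension, 12 months) after the index or pseudo-index date, with zero for people never admitted. Analyse it with the same propensity weights and before/after comparison. State in advance that it combines admission risk and duration and is read as total inpatient burden, not as length of stay.
2. Keep the sub-study 2 HR, but report it as an association among admitted patients. Bring the abstract's wording on effects into line with Study aims and design and with the sub-study 2 aim. State selection by admission and by the 14-day minimum as a limitation.

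The cost is small. Inpatient spell dates are already to be extracted for the cohort, controls already receive pseudo-index dates, and the weights are already planned. The downsides are one more outcome, skewed and with many zeros, and a weaker claim for sub-study 2. The non-parametric bootstrap already planned for costs is one way to obtain intervals for such an outcome.

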## Methods and analysis

### Study setting

Data will be obtained from the South London and Maudsley (SLaM) NHS Foundation Trust. SLaM is one of the largest providers of secondary mental healthcare in Europe, with a diverse catchment area of approximately 1.3 million people who live in the south London boroughs of Lambeth, Southwark, Lewisham and Croydon. Mental health services provided by SLaM include specialist teams for children and adolescents with mental illness and/or neurodevelopmental conditions, community teams for adults, including specialist teams for those with intellectual disability, and mainstream and specialist inpatient wards across different sites. The Trust has implemented a full EHR since 2006, and the SLaM NIHR Maudsley Biomedical Research Centre Case Register contains the clinical records of >5 00 000 patients.^4 5^ Unless otherwise stated, data will be extracted up to an end date of 31 December 2024. The protocol for this study was finalised in July 2025. Data extraction is anticipated to be complete by September 2025 and data analysis by December 2025.

### Data source and linkage

The Clinical Record Interactive Search (CRIS) is a research tool that enables analysis of de-identified EHRs. Patient-level data are extracted from structured fields and through interrogation of unstructured free text (eg, clinical letters and reports) using validated Natural Language Processing (NLP) applications. Available variables include socio-demographic information, neuro-psychiatric signs and symptoms, interventions (medication, psychological therapy), hospital admissions and contacts with professionals and teams (eg, doctors, allied health professionals). We will link data obtained from the SLaM clinical record with Hospital Episode Statistics (HES), a national dataset curated by NHS Digital that includes details of all general hospital inpatient admissions, outpatient appointments and attendances to A&E in England.^6^ Data linkage takes place in a secure data safe haven.^7^

### Natural language processing

NLP is an information extraction technique used to identify relevant information from unstructured free text via automated methods.^8^ NLP models are developed by defining a construct of interest (eg, aggression) and manually annotating examples in a set of training data to classify true positive instances of the construct. Various clinically relevant NLP applications have been developed for use in the SLaM EHR.^9^ NLP-derived data in this study will be obtained as binary variables, which indicate the presence of at least one mention of the construct of interest within a given surveillance period.

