### Identification of C(E)TRs

We will undertake keyword searches in the EHR of people with intellectual disability or autism who meet the study eligibility criteria to identify each community C(E)TR event and the date on which it occurred. Search terms will be ‘Care and Treatment Review’, ‘Care Education and Treatment Review’, ‘CTR’ and ‘CETR’. The search interface does not recognise punctuation or wildcards. We will create a list of people whose health records contain any of these text strings and will review the context of the positive mention to ascertain true instances of C(E)TR meetings, along with the date that the meeting was held. We will label a C(E)TR meeting as having taken place where there is evidence that a meeting has occurred and where a date of the meeting is available. We expect there will be mentions of the search terms which do not correspond to a C(E)TR meeting taking place, for example, where a possible future C(E)TR is flagged. Some mentions of the search terms will be false positives (eg, spe*ctr*um, ECG), and such irrelevant cases will be discounted.

To ensure reliability of identification, two members of the research team will independently review records of 100 eligible patients where C(E)TR search terms have been identified. Cohen’s Kappa will be calculated to test the agreement between the two raters.^10^ If inter-rater reliability is acceptable (Cohen’s kappa >0.6), the raters will work independently and only flag cases that cannot easily be determined. If initial inter-rater reliability is inadequate (Cohen’s kappa <0.6), we will discuss and refine the method of ascertaining whether a keyword mention represents a C(E)TR meeting using a series of test cases. The raters will reconvene periodically to double-review a subset of records to ensure that practice remains consistent. We will retain key excerpts of anonymised text from the EHR as exemplars of mentions of C(E)TRs; a selection of these will be reported for transparency, and the examples can also be used to train any additional members of the research team who interrogate the records.

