### Statistical analysis

#### Descriptive statistics

We will report baseline socio-demographic variables for the C(E)TR and control groups (online supplemental table 1). Frequencies and percentages will be reported for categorical variables and mean (with SD) or median (with IQR) for continuous and count variables, depending on their distributions. We will describe these data separately for two diagnostic categories: (1) People with intellectual disability with/without autism and (2) Autistic people without an intellectual disability. We will compare the C(E)TR to the control group on these baseline socio-demographic characteristics using standard statistical comparisons for categorical (χ^2^) and continuous variables (t-test or Kruskal-Wallis). Descriptives of clinical variables and statistical comparisons between the C(E)TR and control groups will be provided separately for the 6 months before the index date and the 6 months after the index date. These descriptives will not lead to a causal interpretation of the effect of C(E)TRs.

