#### Pre-admission clinical and service use analysis

We will report the clinical and service use variables in online supplemental table 2 for the 6 months before hospital admission and compare variables between those who had a pre-admission community C(E)TR and those who did not. This will also be implemented using standard statistical comparisons for categorical (χ^2^) and continuous variables (t-test or Kruskal-Wallis).

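### Single-mention NLP symptom variables give the C(E)TR group an extra chance of detection where the review's own paperwork is filed, so the secondary symptom comparisons may overstate its symptom prevalence

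*Protocol article*

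**What the plan says.** Under Natural language processing, each NLP item is coded yes or no, by flags "which indicate the presence of at least one mention of the construct of interest within a given surveillance period". Aggression is the example construct. Under Data source and linkage, the free-text data come from "interrogation of unstructured free text (eg, clinical letters and reports) using validated Natural Language Processing (NLP) applications". The article describes no exclusion of document types.

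The Introduction says that a community C(E)TR is convened when admission risk is high, "either because of mental ill-health or because of an escalation in behaviours that challenge". The panel gathers information from the person, family, carers and professionals, and "produces a report and action plan following the C(E)TR with recommendations". Identification of C(E)TRs relies on text in the same record: "We will create a list of people whose health records contain any of these text strings". Raters then review the context to confirm that a meeting took place and to date it.

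In sub-study 1 the index date is the date of the C(E)TR. Descriptive statistics states: "Descriptives of clinical variables and statistical comparisons between the C(E)TR and control groups will be provided separately". The two windows are the 6 months before and the 6 months after that date. The section adds that these descriptives will not be read causally. In sub-study 2, exposure is a community C(E)TR within the 6 months before admission. The pre-admission analysis takes clinical and service use variables over those same 6 months and will "compare variables between those who had a pre-admission community C(E)TR and those who did not", using chi-square and similar tests. Table 1 lists these symptom data among the secondary outcomes of both sub-studies.

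**The concern.** When one mention is enough, a flag depends on how many documents could contain a mention as well as on whether the symptom was present. The exposure adds documents, and their subject matter is the very thing being flagged. Two people with the same symptoms can then score differently because one of them had a review that was written up.

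At stake is the clinical profile of recipients against non-recipients, which is a stated aim of both sub-studies. The Introduction says that this profile may guide work to improve access to C(E)TRs. A gap in symptom prevalence that partly reflects paperwork would misinform that use even with no causal claim attached. The listed strengths and limitations mention missing data and low power, but not unequal opportunity for detection.

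**Working it through.** The protocol states no symptom prevalence, no number of C(E)TRs and no power figure, so there is no figure of its own to reproduce. The check has two parts.

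**1. Where the text falls**

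| | Symptom window | Where C(E)TR text falls |
|---|---|---|
| Sub-study 1, after index | 6 months from the meeting date | The report is written after the meeting, so if filed within 6 months it lies in this window for the C(E)TR group |
| Sub-study 1, before index | 6 months up to the meeting date | Preparatory notes, if filed; some controls may have similar notes |
| Sub-study 2 | 6 months before admission | The meeting lies in this window for every exposed patient and, by definition, for no comparator; the report does too if filed before admission |

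The overlap is clearest in sub-study 2, because one 6-month period defines both exposure and symptoms.

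**2. How large the effect could be**

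All inputs are assumptions:
- p0: probability of at least one mention in ordinary notes, equal in both groups (no true difference).
- q: probability that C(E)TR paperwork is in the record and names the construct, among people with no other mention.

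Prevalence seen in the C(E)TR group = 1 − (1 − p0)(1 − q). Excess over comparators = (1 − p0) × q.

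| p0 | q | C(E)TR group | Excess (points) | Odds ratio |
|---|---|---|---|---|
| 0.10 | 0.2 | 1 − 0.90 × 0.80 = 0.28 | 18 | 3.50 |
| 0.30 | 0.1 | 1 − 0.70 × 0.90 = 0.37 | 7 | 1.37 |
| 0.30 | 0.2 | 1 − 0.70 × 0.80 = 0.44 | 14 | 1.83 |
| 0.30 | 0.5 | 1 − 0.70 × 0.50 = 0.65 | 35 | 4.33 |
| 0.90 | 0.1 | 1 − 0.10 × 0.90 = 0.91 | 1 | 1.12 |
| 0.90 | 0.5 | 1 − 0.10 × 0.50 = 0.95 | 5 | 2.11 |

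With an assumed 50 C(E)TR events and 250 controls (1:5, the top of the matching range), treated as independent, the chance of a nominal p < 0.05 with no true difference is:
- p0 = 0.30: about 17% at q = 0.1, 49% at q = 0.2 and over 99% at q = 0.5.
- p0 = 0.10, q = 0.2: 88%.
- p0 = 0.90, q = 0.5: 15%.

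Two limits follow from the formula. If paperwork names only symptoms already recorded elsewhere, q = 0 and the excess is zero. If comparators also have some such text, with probability q0, the excess shrinks to (1 − p0)(q − q0).

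**The case against.** The strongest reply is that little of importance rests on these variables. Admission, length of stay and HoNOS change are not described as NLP-derived. NLP symptoms are in neither the expected propensity list nor the Cox adjustment list. The sub-study 1 descriptives are expressly non-causal. This stands, and it limits the point to secondary descriptive comparisons. Sub-study 2 carries no such disclaimer, but its symptom comparison is also descriptive.

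Two links in the chain are also unstated. The article does not say that full C(E)TR reports are filed in the Trust's record: a keyword hit needs only a mention of the meeting. Nor does it say whether the NLP applications count historical mentions. They are trained to recognise true positive instances, and many mentions around a review will be real, current symptoms. This makes the size unknown. It does not equalise the opportunity for detection.

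A reader might infer that the flags are switched on in the C(E)TR group only. The document does not support that. Patients for whom a C(E)TR was suggested but not held sit in the sub-study 1 control pool and may have planning notes. Sub-study 2 comparators may have had a C(E)TR more than 6 months before admission, with later text referring to it. They also all went on to an admission of at least 14 days, so their ordinary mention rates may be high and the gap correspondingly small.

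A reader might also infer that the plan will wrongly show no improvement after a C(E)TR. Sub-study 1 compares the groups separately in each window and describes no test of symptom change, so that inference goes beyond the plan.

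**Conclusion.** The point holds in limited form. With single-mention flags, free text that includes reports, and an exposure that generates text on the same constructs, the secondary symptom comparisons can overstate prevalence in the C(E)TR group. This applies to the post-index window of sub-study 1 and the pre-admission window of sub-study 2. It depends on C(E)TR text being filed in the record and naming constructs not otherwise recorded in that window.

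The direction is clear, but the size cannot be determined from the document. In the illustration it runs from 1 point for a construct recorded in nearly everyone to 35 points for one with 30% prevalence and heavy paperwork. Recipients may also be truly sicker, and the planned comparison cannot separate the two. The document gives no ground for extending the point to the primary outcomes, HoNOS change, or NLP symptoms as propensity or Cox covariates. This is a cheap improvement that protects a stated secondary outcome, not a defect in the main analyses.

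**What to change.** - While reviewing search hits, have the raters also tag documents that are C(E)TR reports or preparatory papers. This adds to their present task, which is to confirm and date meetings.
- Present each NLP symptom comparison in both sub-studies with and without the tagged documents, applying the same exclusion to both groups.
- Report the number of documents per person per window by group, and interpret differences in symptom prevalence in that light.
- Treat any adjustment for log document count as optional and exploratory. Note volume partly reflects illness, so it may over-adjust.

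Do not simply drop every document that contains a search term. The protocol itself warns that CTR matches inside the word spectrum, which would remove many ordinary documents in a cohort partly defined by autism. Genuine clinical notes that mention a planned review would also be lost, mostly from the C(E)TR group.

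The cost is a small tagging effort, one extra count per window and, in the sensitivity analysis only, the loss of some genuine mentions found solely in C(E)TR paperwork. In the model above, removing that paperwork sets q to 0 and the artefact to zero at every p0.
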